## Abstract

**Background:**

Although the Brazilian Unified Health System (SUS) offers universal health coverage, access to quality care is often limited by social inequality and location. Although telemedicine has been shown to be an important tool in the efforts to overcome this problem, because it can provide access to specialist care and break the geographical barriers to health care, there are no national studies demonstrating its use in public health.

**Objective:**

This study aims to test the hypothesis that remote consultation can be as effective as standard face-to-face consultation for type 2 diabetes mellitus in the Brazilian public health system and to assess the associated costs related to teleconsultation in public health scenarios, for patients referred from Primary Health Care units of the SUS for specialist care.

**Methods:**

This is a pragmatic, phase 2, unicentric, open-label, noninferiority, blinded allocation, data-blinded, centrally randomized clinical trial. The inclusion criteria will be adults, both sexes, ≥18 years old, glycated hemoglobin (HbA_1c_) ≥8%. Outcomes will be evaluated by assessing symptoms, laboratory exams, anthropometric measurements, blood pressure, adverse events, and satisfaction level for 6 months. The costs of the teleconsultation will be assessed using the time-driven activity-based costing (TDABC) method to compare the costs with the face-to-face consultations. The noninferiority margin was set at 0.5%. Assuming an SD of 1.3% for both groups, true difference between the means of zero, and a type I error level of 5% (one-sided), it was estimated that 117 individuals per group would be necessary to achieve 90% power. Statistical analysis of the efficacy will be done using intention-to-treat and per-protocol approaches.

**Results:**

The results from this trial will be reported according to the CONSORT guidelines. The trial was approved by the institutional review board on October 5, 2019. Data collection started in January 2019 and is expected to finish in 2022. At the time of manuscript submission, 18 participants were recruited.

**Conclusions:**

Our expectations are that providing remote access to health care will result in improvements in the health and quality of life of patients with type 2 diabetes and reduce costs and that both patients and clinicians will benefit from and be satisfied with this technology.

**Trial Registration:**

Registro Brasileiro de Ensaios Clínicos RBR-8gpgyd; https://ensaiosclinicos.gov.br/rg/RBR-8gpgyd

**International Registered Report Identifier (IRRID):**

DERR1-10.2196/23679

## Introduction

According to the 2016 Global Burden of Disease [1], despite the increase in both quality of life and access to health care observed since 1990, there are still many countries in which health inequalities remain, particularly in relation to cancer and noncommunicable diseases, such as asthma, chronic obstructive pulmonary disease, and diabetes. These diseases have a significant impact on quality of life [2], and this is particularly true in the case of diabetes, because it has a range of serious complications in situations where it is poorly controlled by the individual, such as cardiovascular disease, chronic kidney disease, blindness, and lower limb amputation [3], many of which could be avoided by providing better access to health care.

In 2016, Brazil was ranked 96th among 195 countries regarding access to health care and quality of life, according to the Global Burden of Disease [1]. Despite a slight improvement in the health index (from 46.5 in 1990 to 63.8 in 2016), access to health care is still one of the largest indicators of social inequality [4]. While the inhabitants of São Paulo, Brazil’s largest city (Figure 1), have access to 2.81 doctors per 1000 inhabitants, in the northeast region, this proportion is about 1.41 doctors, and in some states, this proportion can even reach <1 doctor per 1000 inhabitants [4]. When considering physicians of all medical specialties, almost 70% of these professionals are concentrated in the south and southeast regions of the country [5]. To improve medical access, there is a need to develop strategies that can not only enhance local primary care but also improve the regulatory processes and the organization of specialized health care in Brazil [6-8].

**Figure 1 figure1:**
[figure not shown]
Regions of Brazil related to this project.

Although there is increasing evidence for the use of remote consultation worldwide [9-11], in Brazil, under Resolution number 1643/2002 [12] of the Federal Council of Medicine, medical consultations by telephone or internet cannot be conducted directly between health professionals and patients. Thus, currently, teleconsulting is only allowed when there is a health professional at both ends of the communication channel, except in the COVID-19 pandemic situation. Also, there are no national studies in Brazil that address the effectiveness and costs involved in teleconsultation service in the public health system. If teleconsulting directly between the physician and the patient can be shown to be safe and effective, this would provide strong evidence to change the current regulations, freeing up one professional from the consultation and driving down costs. The main objective of this study is to test the hypothesis that remote consultation can be as effective as standard face-to-face consultation for type 2 diabetes in the Brazilian public health system and to assess the associated costs related to teleconsultation in public health scenarios.

## Methods

TELEConsult Diabetes is a pragmatic, phase 2, single-center, open-label, noninferiority trial with central randomization that will evaluate the efficacy and safety of specialized remote consultation compared to face-to-face consultation in patients with type 2 diabetes mellitus referred by primary health care units to specialist care in the Unified Health System (SUS) [13].

The inclusion criteria are adults of both sexes, ≥18 years old, established diagnosis of type 2 diabetes, and either not insulin dependent (with any level of glycemic control measured by glycated hemoglobin [HbA_1c_] accordingly to local protocol [14-17]) or insulin dependent (HbA_1c_ >8%). Exclusion criteria are patients <18 years old or with type 1 diabetes, women with gestational diabetes or diagnosed during pregnancy, and patients with chronic renal failure with estimated or measured creatinine clearance <30 mL/min/m^2^ [18].

Brazil has a universal public health care system called SUS, which is structured around the principle of primary care and operates by integrating other services and levels of care, such as specialized care, into the system for the whole population. The main goal of primary care in Brazil is to provide basic care and to coordinate other levels of care throughout the health system network, regulating referrals to specialist care [8].

The Telehealth Center of Santa Catarina state uses a system that does not represent the reality in most Brazilian states. First, the primary care physicians request a teleconsultation with a specialist. This consultation involves both the primary care physicians and the specialist. Following this first contact, the primary care physician decides whether the patient needs to be referred to a face-to-face consultation with the specialist [19,20]. This system of compulsory flow established and operating in Santa Catarina state is the ideal setting to investigate the potential of remote consultation in primary health care, compared to face-to-face consultations.

The participant will be identified by the primary care physician and the Telehealth Center of the state of Santa Catarina, and the regulatory department of the Municipal Health Office of Joinville will determine if she or he meets the eligibility criteria. Patients with type 2 diabetes mellitus may be recruited from any of the city’s 70 primary care centers. A researcher will contact the patient by telephone to tell them about the trial and invite them to participate in the study. If the patient agrees, they will be told that they need to provide their written consent, and an informed consent form will be posted to them prior to reading and assessment for their participation in the study. Then, 2-5 days after sending the informed consent form, the researcher will again telephone the patient to confirm their interest in participating in the trial. If the response is still positive, they will schedule a home visit at a convenient time with the patient, in the presence of a legal representative or relative if they so wish. During the visit, any questions related to the study will be answered. After signing and agreeing to participate in this study, the researcher will tell the participant about the next steps: Their data will be randomized in a system created especially for this trial, and they will be scheduled for a face-to-face consultation or for a remote consultation with the specialist. By the end of this home visit, the participant will have been advised about the study, their participation, the date and place of the research consultation, and that there are no costs involved.

To calculate the real cost of a teleconsultation service to compare with the cost of the face-to-face service and to generate a cost parameter for the primary health care units for this type of service, the time-driven activity-based costing (TDABC) method will be used [21,22]. In addition to the costs of the resources used, this method also considers the amount of time spent on each stage of the process, enabling the identification of stages where the teleconsultation speeds up or slows down the process, reducing or increasing costs in relation to face-to-face consultation.

This study will also include other indicators, such as the transportation costs for the patients and physicians in a “real-word” scenario, to carry out cost-effectiveness estimates. Finally, we intend to discuss issues related to the reduced costs that increased access to medical care, via teleconsultation, can generate for the system.

The randomization list will be generated electronically using appropriate software. Randomization will be performed in blocks of 4 at a 1:1 ratio. Confidentiality of the randomization list will be ensured by setting up a central database and the use of an electronic case report form. Access to the system will be granted through specific usernames and passwords given to each investigator or study team. The patient will be allocated to one of the treatments (remote consultation or face-to-face consultation) only after being registered in the system. Given the nature of the intervention, blinding is not feasible. However, data analysis will be performed by a statistician blind to patient allocations.

Participants in both groups will be assisted by 1 of a team of 4 endocrinologists from the public outpatient clinic. They will take turns to provide assistance in the 2 modalities. The remote consultation with the intervention group will involve only the specialist and the participant. These consultations will take place in 1 of the 6 primary care units chosen to cover the main regions of the city. In each of these units, the research team set up a room with a computer, microphone, and camera to deliver the remote consultation, assisted by the same team of endocrinologists.

The same physicians will undertake both the remote consultation and the face-to-face consultation, with the same duration (30-60 minutes). All the physicians are specialists medically trained in endocrinology and experienced in caring for patients with diabetes in different settings and as part of the city’s specialist care network. A protocol based on national and international guidelines specifically designed for the study [17,23-25] will be used to ensure that all the consultations are as similar as possible. The physicians were instructed to follow the protocol to avoid any bias related to the consultation. The protocol includes instruction on the questions to be asked about the participant’s health and the medicines they are using, the scale to be used for hypoglycemia evaluation [26], and the medications to be prescribed (following current guidelines). At the end of the consultation, participants from both groups receive, in addition to medical advice and drug prescriptions, guidance on any laboratory tests that need to be carried out before the next consultation.

The primary outcome will be a change in HbA_1c_ levels at 6 months after randomization. However, we will perform a prespecified analysis 3 months after randomization.

Secondary outcomes will be fasting blood glucose, complete blood count, urea, creatinine, total cholesterol, triglycerides, high-density lipoprotein cholesterol, low-density lipoprotein cholesterol, systolic and diastolic blood pressure, body weight, BMI, frequency of hypoglycemia, and incidence of adverse events. In addition, in the intervention group, we intend to evaluate the satisfaction of the endocrinologists and the patients with the video conference system using a structured questionnaire [23].

A specific quality of life in diabetes questionnaire will be used with patients with diabetes mellitus in the first and last research consultations in both groups [27-29]. In addition, we will estimate the actual cost of the remote consultation service, using the TDABC method [21,22] to obtain the unit cost of remote consultation in the primary health care units.

This trial is registered with the Ethics and Research Commission (03434218.1.2001.5362).

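### A single published block size of 4 in a single-center, open-label trial weakens allocation concealment: up to one third of assignments could be deduced by a recruiter who tracks earlier ones

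*Protocol article*

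**What the plan says.** The abstract describes the study as an "open-label, noninferiority, blinded allocation, data-blinded, centrally randomized clinical trial". The Methods section calls it a "single-center, open-label, noninferiority trial with central randomization".

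On the sequence itself, Methods says "The randomization list will be generated electronically using appropriate software" and then "Randomization will be performed in blocks of 4 at a 1:1 ratio". One list is referred to. No stratification factor and no second block size is given.

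On protection, Methods says "Confidentiality of the randomization list will be ensured by setting up a central database and the use of an electronic case report form". Access is by individual username and password, and a patient receives an arm "only after being registered in the system". Of masking after allocation it says "Given the nature of the intervention, blinding is not feasible"; only the statistician is blinded.

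On recruitment, Methods describes this order: the municipal regulatory department settles eligibility; a researcher telephones, posts the consent form, telephones again 2–5 days later and arranges a home visit; consent is signed at the visit. By the end of that visit "the participant will have been advised about the study, their participation, the date and place of the research consultation". Remote consultations are held in one of six equipped primary care units. Patients may come from any of 70 primary care centers.

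Results gives 124 participants per group, with 18 recruited when the article was submitted.

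**The concern.** A central, password-protected list stops anyone from reading ahead. It does not stop anyone from counting. In a 1:1 block of 4, once two patients have gone to one arm the rest of the block is settled. The ingredients for counting are a known block size, which is printed here, and sight of past assignments. An open-label trial offers that sight, and the home-visit description suggests it, because the place of consultation points to the arm.

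The researcher also has some influence over order of entry, through the timing of the second call and of the visit and through the effort put into persuasion. All of this comes before randomization and needs no say over eligibility. A recruiter who expected a particular arm next could bring forward or hold back a patient.

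At stake is the comparability of the arms. The primary noninferiority comparison is a difference in mean HbA1c change with a 90% confidence interval, supported by an ANCOVA whose only covariate is baseline HbA1c. Selection on other prognostic features would stay in the estimate. It could favour remote care and make a false noninferiority claim more likely, or work in the opposite direction.

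**Working it through.** **Inputs from the protocol article.** Block size 4, ratio 1:1, one list, no strata stated (Methods). 124 per group, so 248 in total; 18 recruited at submission (Results).

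**The plan's own figures.** The article gives no predictability figure. Its sample size reproduces: with margin 0.5, SD 1.3, true difference 0 and one-sided 5%, the noncentral t gives power 0.8990 at 116 per group and 0.9012 at 117. Then 117 / 0.95 = 123.2, rounded up to 124. The total of 248 is 62 blocks of 4.

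**Certain allocations when every earlier assignment is seen.** There are 6 equally likely blocks (the arrangements of AABB).
- AABB and BBAA: positions 3 and 4 are both determined, so 2 certain.
- The other four: only position 4 is determined, so 1 certain.
- Mean per block = (2 × 2 + 4 × 1) / 6 = 4/3. Share = (4/3) / 4 = 33.3%.
- Whole trial: 248 / 3 ≈ 83. Still to come at submission: 248 − 18 = 230, and 230 / 3 ≈ 77.

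**Best guess (always name the arm that is behind in the block).** The probability of being right is 1/2 at position 1 and 2/3 at position 2. At position 3 it is 1/3 × 1 + 2/3 × 1/2 = 2/3, and at position 4 it is 1. The sum is 2.833, and 2.833 / 4 = 70.8%. Unrestricted randomization would give 50%.

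**Partial sight.** Suppose the recruiter knows the position in the block but sees each earlier assignment only with probability *f*. The document does not give *f*, so a range is assumed. A slot is certain only if both earlier members of the completed arm were seen, so the share is (1/3 × *f*² + *f*²) / 4 = *f*² / 3.

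| *f* | Certain share | Of 230 |
|---|---|---|
| 1.00 | 33.3% | 77 |
| 0.75 | 18.8% | 43 |
| 0.50 | 8.3% | 19 |
| 0.25 | 2.1% | 5 |

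**After a change to random block sizes.** Simulated trials of 248, with an observer who sees every past assignment and knows which sizes are possible:

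| Sizes | Certain | Best guess right |
|---|---|---|
| 4 only | 33% | 71% |
| 4 or 6 | about 5.5% | about 69% |
| 4, 6 or 8 | about 2.3% | about 68% |
| 6 to 14 | below 1% | about 65% |

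Varying the size removes most of the certainty but only a little of the guessing.

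**The case against.** The strongest reply is that the article already has real safeguards. The list is central and password-protected, consent and registration come before allocation, and a separate body decides eligibility. Even in the worst case two thirds of assignments are not certain. A reader might infer that the concealment claimed in the abstract is simply not delivered. The document does not support that; it supports only that concealment is weakened.

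A reader might also infer that the recruiter will know one third of what comes next. That figure is a ceiling. It needs one person who knows where each block starts and sees every earlier assignment in order. The article does not say how many researchers recruit or what each of them sees, and patients come from up to 70 centers. The statement about the consultation place is in the passive, so it suggests that the recruiter learns the arm without saying so. Recruitment also takes several days per patient, so using a foreseen slot requires that nobody else is registered first. These points stand, and they are why a range is shown.

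A third tempting step is to assume a prognostic gap between steered patients and express the bias as a share of the 0.5 margin. The document gives no source for such a gap, for how often steering would succeed, or for its direction. No bias figure is defensible.

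Finally, a condensed article may omit stratification or a rule withholding the block size from recruiters; the words fixed and single list are not used. That is fair, but the point does not rest on silence alone. One small block size is stated, and it is stated in a public article while most allocations were still to come.

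**Conclusion.** The point holds as a weakness created by a stated rule. One published block size of 4, on what appears to be one unstratified list in an unmasked single-center trial, makes up to 33% of allocations deducible and up to 70.8% guessable. That is about 77 certain assignments among the roughly 230 outstanding at submission. The upper figure assumes full knowledge of block starts and past assignments; with sight of 75% to 25% of them the certain share is about 19% to 2%. The effect on the HbA1c comparison cannot be quantified from the document, and nothing in it shows that steering occurred or would occur. The change is worth making because it costs little, not because a bias has been demonstrated.

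**What to change.** For all participants not yet randomized, regenerate the electronic list with randomly varying block sizes. Keep the sizes in a restricted document and do not disclose them to anyone who recruits. Say publicly only that permuted blocks of varying, undisclosed size are used from that point. Keep the existing order of consent and registration before allocation, which is already right. Assignments already made stay as they are.

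The gain is mainly in certainty: from up to 33% down to roughly 2–6% with sizes 4/6 or 4/6/8, even if that set became known. Best-guess accuracy falls only to about 65–69%, the lower end needing larger blocks, so the change should not be presented as making allocation unpredictable.

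The cost is one regeneration of the unused list and a possible final imbalance. With sizes up to 8, an unfinished last block can leave the arms 4 apart, and the block that is half used after 18 patients can add 2. The information retained is 1 − (6 / 248)² = 99.9%, so the planned sample size does not change.

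### The first quality-of-life questionnaire is taken after allocation, so it is not a pre-allocation baseline, and any comparison that uses it is at risk of bias

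*Protocol article*

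**What the plan says.** All of this is in the Methods of the protocol article unless noted.

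- **Consent visit.** A researcher visits the participant at home to obtain consent. After signature the participant is told what follows, which the article puts thus: "Their data will be randomized in a system created especially for this trial, and they will be scheduled for a face-to-face consultation". The alternative is a remote consultation. The visit closes with the booking known: "By the end of this home visit, the participant will have been advised about the study, their participation, the date and place".
- **Allocation and blinding.** A patient is allocated "only after being registered in the system". The article adds: "Given the nature of the intervention, blinding is not feasible". Only the statistician is blinded.
- **Setting.** Remote consultations are held in one of six equipped primary care units.
- **Quality of life.** The questionnaire "questionnaire will be used with patients with diabetes mellitus in the first and last research consultations in both groups". No other quality-of-life measurement is described.
- **Analysis (Results section).** Mixed repeated-measures models, with baseline as one of the time points, are to be considered for continuous secondary endpoints. No analysis specific to quality of life is given.

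**The concern.** A baseline is useful because allocation cannot have influenced it. Here the early score comes after the arm has been assigned and, in all likelihood, after the participant knows it. A self-reported score can respond to satisfaction or disappointment with the assigned arm, and to the setting in which the form is filled in. Blinding the statistician does nothing about that.

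If such a reaction differs between arms, an analysis that subtracts the first score or adjusts for it carries the reaction, with its sign reversed, into the estimated effect. On a scale where higher is better, disappointment at being sent to one arm lowers that arm's first score and makes its later improvement look larger. Enthusiasm does the opposite.

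Quality of life is one of the benefits that the abstract's Conclusions and the Discussion expect from remote access, so readers will look at this result.

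**Working it through.** **1. Order of events.** Put together, the Methods give: signature at the home visit; randomization; booking to an arm-specific consultation, with date and place known by the end of the visit; first consultation with first questionnaire; last consultation with last questionnaire. The first score therefore follows allocation. That the participant knows the arm is an inference from the booking and the absence of blinding. Someone who did not know it at home would learn it on arriving at the consultation.

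**2. The article's own figures.** There is none for quality of life. The sample size for HbA1c (margin 0.5%, SD 1.3%, true difference 0, one-sided 5%, 90% power) reproduces. Power by the noncentral t distribution is 0.8990 at 116 per group and 0.9012 at 117, and 117 / 0.95 = 123.2, which rounds up to 124. Nothing below changes this.

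**3. Bias from a shift in the first score only.** Let the true effect be zero, let d be the shift in the remote arm's first score relative to the other arm, and let b be the within-arm slope of the last score on the first.

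- Difference in change: 0 - d = **-d**.
- Baseline-adjusted difference: 0 - b × d = **-b × d**.
- Difference in last scores alone: **0**.

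The article gives neither d nor b, so the ranges are assumptions: d from 0.1 to 0.3 SD, and b from 0.3 to 0.7 (equal to the first-last correlation when the two SDs are equal). A simulation in SD units with 400,000 participants per arm gave:

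| b | d | Change | Baseline-adjusted | Last score only |
|---|---|---|---|---|
| 0.3 | 0.1 | -0.101 | -0.029 | 0.002 |
| 0.5 | 0.2 | -0.199 | -0.099 | 0.001 |
| 0.7 | 0.3 | -0.300 | -0.211 | -0.003 |

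These agree with the formulas. If d = 0, the bias is zero.

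**4. Bias from a shift present at both visits.** If the setting or mode of administration moves the score by the same d at the first and last consultation:

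- Difference in change: d - d = **0**.
- Baseline-adjusted difference: d - b × d = **d(1 - b)**, for example 0.5d at b = 0.5.
- Difference in last scores alone: **d**.

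So the two kinds of shift call for opposite analyses. Change scores remove a constant mode effect but carry a reaction confined to the first visit. Last scores do the reverse. If both occur, neither analysis is clean.

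**The case against.** The strongest reply is that the documents show no bias. It needs a shift that differs between arms, for which the article gives neither size nor direction, and an analysis that uses the first score, which the article does not specify. It never calls this score a baseline. The mixed models are only to be considered, and for endpoints measured at three times, whereas quality of life is measured twice and stands apart from the main list of secondary outcomes. If the form is completed before contact with the specialist, only knowledge of the arm and the setting can act on it, not the care itself. All of this stands, and it limits the point to a risk.

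Three stronger readings are tempting and are not supported.

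- *The quality-of-life comparison is biased.* A reader might infer this from the order of events, but that order shows only that the first score is unprotected.
- *The form is given by video in one arm and in person in the other.* The article does not say who gives it, in what form, or at what moment. Remote participants attend a health unit in person, so a paper form is equally possible.
- *Baseline blood pressure and weight suffer in the same way, because no one is in the remote room to measure them.* The sentence "The remote consultation with the intervention group will involve only the specialist and the participant" describes who takes part in the consultation. It does not say who takes measurements, where, or with what device.

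What the reply does not remove is the order itself. With two measurements, the first is the only one available as a baseline, and a researcher already sees the participant before randomization.

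**Conclusion.** The point holds as a risk that is cheap to remove. The first quality-of-life score is not a pre-allocation baseline, and a change-from-baseline or baseline-adjusted comparison built on it is open to bias of -d or about -b × d from a shift confined to that score. Under the assumed ranges this is 0.1 to 0.3 SD for change and about 0.03 to 0.21 SD after adjustment. These figures illustrate the mechanism and are not estimates for this trial. The conclusion rests on two assumptions: that participants know their arm when they answer, and that the analysis uses the first score. The noninferiority test on HbA1c and the sample size are untouched.

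**What to change.** - **Baseline.** Give the quality-of-life questionnaire at the consent home visit, after signature and before randomization is carried out in the system, whoever carries it out.
- **Final questionnaire.** State how it is given and by whom, and do it in the same way in both arms, so that a mode effect does not take the place of the problem just removed.
- **Participants already enrolled.** Flag their first score as post-allocation, and compare final scores without relying on it. That comparison remains open to any setting effect at the last visit, which should be acknowledged.

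The cost is a few minutes at a visit that already takes place, a change in the order of procedures, and a different kind of baseline for those already enrolled. The article reports 18 recruited when the manuscript was submitted, of 2 × 124 = 248 planned (18 / 248 = 7%). At that stage nearly all participants could still have followed the new order.
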